### Impact and outcome evaluation

Differences in individual and community-level impacts and outcomes will be measured using a cross-sectional design with differences between intervention and comparison groups assessed at the cluster (school, workplace, community) level as appropriate. Trained research staff (supported by project staff at baseline) will collect the anthropometric, behavioral, quality of life and environmental data from each school/workplace pre- (2008/9) and post- (2010) intervention activities. Data on socio-demographics will also be collected in two ways: direct data collection from the participant (age, gender, country of origin, residential address, school address) and from the community (region) using the 2006 ABS Census data (e.g. mean income, education, occupation, indigenous status, family structure, country of origin, English-speaking). This community level data will be used in hierarchical linear modeling to analyze the outcomes of the interventions. At the local level, additional intervention impacts will be captured through qualitative methods (narrative evaluation, case studies, photo diaries etc).

### Anthropometry

Weight, height and waist circumference will be measured by trained researches in accordance with standard methods for the collection of anthropometric data [18]. All measurements will be taken in light clothing (one layer), without shoes, with all jewellry removed and pockets emptied. Cultural and body image sensitivities will be accommodated using previously published strategies [19]. Weight will be measured to the nearest 0.05 kg using electronic scales (A&D Personal Precision Scale UC-321). Height will be measured using a portable stadiometer to the nearest 0.1 cm (PE87 portable stadiometer) and participant hair styles which may interfere with the measurement process will be removed or adjusted. Participants will be instructed to stand with their weight distributed evenly on both feet, with their heels together and arms hanging freely by their sides. Four contact points between the participant's body and the measuring apparatus will be required (head, upper back, buttocks and heels) and the head aligned in the Frankfurt plane prior to the measurement being taken. Waist circumference will be measured to the nearest 0.1 cm at the end of a normal expiration on the horizontal line of the umbilicus using a standard flexible seamstress measuring tape for students and a constant tension tape figure finder for adults. Two measurements will be recorded for each parameter, and where there is a disagreement between two measurements (>0.1 kg for weight, >0.5 cm for height and >0.3 cm for waist circumference), a third will be taken. The mean of all measures will be used for analysis, and Body Mass Index (BMI) (weight in kg/height in m^2^) will be calculated to classify child and adult weight status using the International Obesity Task Force age-specific BMI cut-off points [20]. The scales and stadiometer will be re-calibrated every 1000^th ^student measured and the flexible measuring tape verified against a designated 1 m metal ruler on a weekly basis to confirm the tape has not stretched.

### Survey methodology

Surveys capturing information regarding nutrition and physical activity behaviors will be piloted and subsequently administered to all students in grade four and higher, and to all adults. Surveys will be based on those used in our previous and similar studies [12] and http://www.goforyourlife.vic.gov.au/hav/articles.nsf/practitioners/Be_Active_Eat_Well_Final_Reports?Open) and aligned with state-wide surveillance measures where possible.

### Nutrition and physical activity behaviors

The behavioral surveys will contain 20 to 30 questions primarily focusing on the types and amounts of foods eaten on the previous day and the type, frequency and duration of sedentary behaviors and physical activity. Age-appropriate surveys will be used for younger and older children and adults.

### Quality of life

Secondary school students and adults will also complete the Assessment of Quality of Life (AQoL) mark 2 [21,22], a 20 item quality of life assessment tool comprising six dimensions: physical ability, social and family relationships, mental health, coping, pain and physical senses (vision, hearing and communication). Scores from the six dimensions will be combined to calculate an overall quality of life rating. The AQoL, is a utility-based instrument originally developed for Australian adults, which has now been recalibrated for use with adolescents ([name], personal communication, manuscript under review).

### School environment

An assessment of the school environment will be conducted by a trained researcher with one to three school staff to complete a questionnaire designed to capture seven key elements of the school: demographics, internal and external food services, food/nutrition and physical activity policy(ies); nutrition environment; and the physical activity environment. The questionnaire is based on similar instruments that have been developed and used for environment audits [23] and a consensus answer will be recorded for each question.

### Measures of deprivation and ethnicity

The postcode of each participant will be used to determine the SEIFA This is an area-level indicator of socio-economic status, with a low score on the SEIFA indicating an area of social disadvantage and a higher score an area less disadvantaged [17]. Information related to ethnicity and length of time since migration to Australia will also be collected.

### Data entry, handling and statistical analysis

The child behavioral surveys will be scanned directly into an electronic database. The demographic, other survey (adult behavioral and AQoL) and anthropometric data will be double-entered into Stata (Version 10.1, StataCorp, College Station, Texas, USA). All statistical analysis on individual and school environment data will be conducted using Stata and quantitative analysis of the cross-sectional impact and outcome data will utilize regression analysis, hierarchical linear modeling, descriptive statistics and design corrected chi^2 ^analysis, as appropriate. The SVY commands in stata will be used for all analysis to account for clustering and design effects and the primary analysis will be between the intervention and comparison groups post-intervention. Demographic data will be used to adjust for confounding (e.g. gender; socio-economic status), and additional data on smoking status and alcohol intake will be collected from adults. Qualitative data will be analyzed using content and inductive thematic methods, as appropriate. Data triangulation and mixed methods analysis will also be used where possible.

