### Sample size

The sample size calculations were primarily designed to account for intervention outcomes and detect a meaningful level of change compared to the comparison group. As such, calculations were based on a difference in behavior prevalence of > 15% and zBMI > 0.15 units between intervention and comparison groups, while also accounting for the design effects of clustering by schools and workplaces. Detecting differences within this design will require a sample of approximately 5,200 students (approximately 2,400 primary students and 2,800 secondary students). For the adult sample, 245 people in the intervention and a matched comparison sample will have the power to detect a 13 percentage point difference in behavioral outcomes (power of 80%) and difference of 1.7 BMI units between intervention and comparison samples with 80% power at a significance level of 0.05.

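### Stata SVY commands are prescribed for all analysis with no small-sample correction; if workplaces or schools are few and unequal in size, the default SVY test rejects too often

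*Protocol article*

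**What the plan says.** The section Data entry, handling and statistical analysis lists "regression analysis, hierarchical linear modeling, descriptive statistics and design corrected chi"-squared analysis, to be chosen as appropriate. It then sets a general rule: "The SVY commands in stata will be used for all analysis to account for clustering and design effects". The same sentence continues that "the primary analysis will be between the intervention and comparison groups post-intervention", so the rule covers the main result. No variance estimator, stratum, primary sampling unit or degrees-of-freedom rule is named.

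The section Impact and outcome evaluation describes the analysis differently, with "differences between intervention and comparison groups assessed at the cluster (school, workplace, community) level as appropriate". On the census variables it adds: "This community level data will be used in hierarchical linear modeling to analyze the outcomes of the interventions".

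The Sample size section gives "For the adult sample, 245 people in the intervention and a matched comparison sample" for adults, "with 80% power at a significance level of 0.05", and about 2,400 primary and 2,800 secondary students. It says clustering by schools and workplaces was allowed for, but gives no number of clusters, ICC or design effect. Table 1 lists working adults as the primary target in community 5 only. The Comparison groups section matches schools and workplaces on size, among other things.

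**The concern.** The default SVY variance is built from the spread of cluster residual totals around the group mean. A large cluster pulls that mean towards itself, so its residual is too small exactly where its weight is greatest. With many clusters this hardly matters. With few clusters of unequal size the standard error is biased low, and the survey t reference (clusters minus strata) does not repair it.

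The general rule therefore puts the stated 0.05 level at risk where clusters are fewest, which is probably the adult sample. Intervals would be too narrow, and a chance difference between a handful of workplaces could be reported as an intervention effect. The article also names hierarchical models and cluster-level assessment. These give different standard errors, and nothing says which one supplies the reported p-value.

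**Working it through.** **1. Can the cluster count be recovered from the plan's own figure?** Take the adult target: 245 per group, 13 percentage points, 80% power, alpha 0.05 (two-sided and 1:1 assumed). The formula for two proportions is n = [1.96√(2p̄(1−p̄)) + 0.842√(p₁(1−p₁)+p₂(1−p₂))]² / 0.13². The continuity-corrected value is (n/4)[1+√(1+4/(0.13n))]².
- 0.50 v 0.63: n = 228, corrected 243.
- 0.40 v 0.53: corrected 246.
- 0.435 v 0.565: corrected 247.

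So 245 is reproduced near a 50% base rate with no design effect. The base rate is not stated, however. At 0.10 v 0.23 the corrected n is 142, which leaves room for a design effect of 245/142 = 1.7. For BMI, n = 2(1.96+0.842)²SD²/1.7² gives 245 at SD about 6.7 with no design effect, or 136 at SD 5, and 136 × 1.8 = 245. The figures fit several designs, so cluster number and size cannot be read from them and have to be assumed.

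**2. Inputs.**
- From the article: the SVY rule, alpha 0.05, and 245 adults per group.
- Assumed: 3 to 30 clusters per group (k), ICC 0.02-0.05, CV of cluster size 0, 0.6 or 1.0.
- For scale, 245 adults in 5, 10, 20 or 30 workplaces is on average 49, 24.5, 12 or 8 per workplace.

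**3. Variance formulas.** Let u_j be the sum of residuals from the group mean in cluster j, divided by the group size, and let K = 2k.
- One stratum: V = K/(K−1) · Σu_j², t on K−1 df.
- Group as stratum: V = Σ over groups of k/(k−1) · Σu_j², t on K−2 df.

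With equal sizes, Σu_j² has expectation (1−1/k) times the true variance. The stratified factor k/(k−1) corrects this exactly. The one-stratum factor does not: at k = 5 it leaves (10/9)(4/5) = 0.89 of the variance, or √0.89 = 0.94 of the standard error. With unequal sizes neither factor is enough.

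**4. Simulation under no effect** (individual-level difference in means, gamma-distributed cluster sizes, 6,000 runs per cell, Monte Carlo error about 0.3-0.5 points). The entries are the percentage of nominal 5% tests that reject, over ICC 0.02-0.05.

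| Clusters per group | Size CV | One stratum | Group as stratum |
|---|---|---|---|
| 5 | 0 | 6.5-6.8 | 4.9-5.4 |
| 5 | 0.6 | 8.8-9.3 | 6.9-7.1 |
| 5 | 1.0 | 13.4-14.2 | 11.4-11.6 |
| 10 | 0 | 5.3-5.7 | 4.6-5.0 |
| 10 | 0.6 | 6.3-7.7 | 5.6-6.9 |
| 10 | 1.0 | 8.7-10.9 | 7.9-10.1 |
| 20 | 0.6 | 6.1-6.5 | 5.7-6.0 |
| 20 | 1.0 | 7.7-8.2 | 7.4-8.0 |
| 30 | 0.6 | 5.4-5.6 | 5.1-5.4 |
| 30 | 1.0 | 6.6-7.2 | 6.3-6.9 |

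At the extreme, 3 per group with CV 1.0 gives 18-20% (12.5-14.8% with group as stratum), and the mean standard error is about 0.60 of the true one.

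**5. Alternatives.**
- A bias-corrected cluster-robust variance with Satterthwaite df, run with 245 per group, held about 4-6% in every cell tried. The point estimate is unchanged.
- An unweighted t-test on cluster means held 3.7-5.9% with equal numbers of clusters. It fell to about 2-3% with 5 v 15 clusters of unlike mean size. At ICC 0.02 and CV 1.0 its estimate had about 1.3 times the variance of the individual-level estimate with 10 clusters per group, and 1.5 times with 20.

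**The case against.** The strongest reply is that the premise is not in the document. No cluster count, ICC or size spread is given, and linearised variance is only the software default; the article names no estimator. Declaring group as stratum is an ordinary SVY set-up and brings the rate to about 5% when sizes are equal. Variance estimator and degrees of freedom are also details that a condensed article commonly leaves to an analysis plan. All of this stands, and it is why the point is conditional.

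Three stronger readings are tempting, and the document supports none of them.
- A reader might infer that the plan locks in an invalid test with a known error rate. The rates above belong to the assumed grid and run from about 5% to about 20%.
- A reader might infer that the adult sample comes from a few workplaces in one rural community. Table 1 makes this plausible, but the Sample size section does not say where the 245 are recruited, and other communities list adult groups as secondary targets. No school count is given either.
- A reader might infer a flat contradiction between the two analysis sections. Both use as-appropriate wording and both name hierarchical models, so this is loose wording to reconcile.

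The objection does not remove the rule itself. The article does more than leave the method open: it prescribes SVY for all analysis, the primary comparison included. Stratifying by group does not cure unequal sizes, since at CV 1.0 with 5 per group the rate is still 11.4-11.6%.

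**Conclusion.** The point holds in conditional form. If the default SVY variance is used, and if clusters are fewer than about 20 per group and unequal in size, the nominal 5% test is anti-conservative. Across both stratum set-ups the rate is about 7-14% with 5 clusters per group, 6-11% with 10 and 6-8% with 20. This rests on assumed ICC 0.02-0.05 and size CV 0.6-1.0. The limit of 20 is a working guide, not a threshold: at CV 1.0 some excess remains even at 30 per group.

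The exposure is most plausible for adults. Whether it arises at all depends on cluster numbers and sizes that the article does not give. This is a worthwhile, inexpensive improvement to a stated method, and it does not show that the planned results will be wrong.

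**What to change.** For the intervention-versus-comparison tests, keep the same regression but take standard errors, intervals and p-values from a bias-corrected cluster-robust variance with Satterthwaite degrees of freedom. Do this at least for adults and for any stratum with few clusters. Where clusters are many it converges to ordinary SVY output, so it can safely be applied throughout.

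A t-test on covariate-adjusted workplace or school means, which the Impact and outcome evaluation section already permits, can serve as a sensitivity analysis. It weights clusters rather than individuals, so it can target a different average and is not an equivalent substitute.

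Reword the SVY sentence so that it agrees with the hierarchical modelling and cluster-level assessment named in the two sections, and say which analysis supplies the reported p-value.

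The cost is a sentence or two of text, a little more analysis work and somewhat wider intervals. No further data are needed.

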## Abstract

**Background:**

There is only limited evidence available on how best to prevent childhood obesity and community-based interventions hold promise, as several successful interventions have now been published. The Victorian Government has recently funded six disadvantaged communities across Victoria, Australia for three years to promote healthy eating and physical activity for children, families, and adults in a community-based participatory manner. Five of these intervention communities are situated in Primary Care Partnerships and are the subject of this paper. The interventions will comprise a mixture of capacity-building, environmental, and whole-of-community approaches with targeted and population-level interventions. The specific intervention activities will be determined locally within each community through stakeholder and community consultation. Implementation of the interventions will occur through funded positions in primary care and local government. This paper describes the design of the evaluation of the five primary care partnership-based initiatives in the *'Go for your life' Health Promoting Communities: Being Active Eating Well *(HPC:BAEW) initiative.

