### Evaluation design

The evaluation design will be quasi-experimental, repeat cross-sectional, with outcomes compared between intervention and comparison areas at two time points within the project duration (2008/9 and 2010). The socio-ecological model of health has been utilized to develop the intervention activities and evaluation design. This framework focuses attention on five key determinants of health behavior: individual factors, interpersonal and primary groups; institutional and organizational factors, community factors and public policy [15]. The model assumes that appropriate changes in the social environment will produce changes in individuals and the support of individuals in the population is essential for implementing environmental changes [16]. Consistent with this framework, impact and outcome data will be collected at the community, setting and individual levels. Table 3 provides an overview of the evaluation data to be collected.

**Table 3 T3:** Overview of the multi-level and mixed methods evaluation data to be collected

Level	Details	Tools
**Community**	Networks and partnerships Opportunities for physical activity Access to nutritious food Policy development and implementation Capacity building	Partnership/community assessment Document analysis Key informant interviews (post intervention)
**Workplace**	Environment Access to healthy food Opportunities for physical activity Policy development	Environment assessment Document analyses
**School**	Socio-cultural environment Policy development and implementation Capacity building Access to nutritious food Opportunities for physical activity	School environment assessment
**Individual**	Food and activity related behaviors Weight status Quality of life	Health behavior questionnaire Anthropometric Assessment Quality of Life Questionnaire

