### Comparison groups

Appropriate comparison groups for each target (age) group will be selected from across the state. Comparison schools will be randomly drawn from Victorian schools matched on demographics including school type (government/non-government), school size, level of disadvantage (using the Socio-Economic Index for Areas [SEIFA] index of advantage/disadvantage Victorian decile from the 2006 Census [17]) and location (Local Government Area and region). Comparison workplaces will be matched on the demographic characteristics of the intervention workplaces, including the workplace size, type and location.

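### The primary analysis compares non-randomised groups after the intervention, with no stated use of the 2008/9 outcome data, so residual pre-existing differences enter the effect estimate

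*Protocol article*

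**What the plan says.** - **Primary contrast** (Data entry, handling and statistical analysis): "the primary analysis will be between the intervention and comparison groups post-intervention". The same section adjusts for demographic confounders, giving gender and socio-economic status as examples.
- **Design** (Evaluation design): "The evaluation design will be quasi-experimental, repeat cross-sectional, with outcomes compared between intervention and comparison areas at two time points".
- **Data collected** (Impact and outcome evaluation): anthropometric, behavioural and quality-of-life data, and "environmental data from each school/workplace pre- (2008/9) and post- (2010) intervention activities". Census variables for the community also enter hierarchical models.
- **How the intervention communities arose** (Abstract, Background): "The Victorian Government has recently funded six disadvantaged communities across Victoria, Australia for three years". Five of the six are evaluated here.
- **How comparators are chosen** (Comparison groups): "Comparison schools will be randomly drawn from Victorian schools matched on demographics including school type (government/non-government), school size, level of disadvantage", and location. For adults: "Comparison workplaces will be matched on the demographic characteristics of the intervention workplaces, including the workplace size, type and location".
- **Effect sizes** (Sample size): the opening sentence speaks of power to "detect a meaningful level of change compared to the comparison group". The next sets the student targets as between-group differences of 15% in behaviour prevalence and 0.15 in zBMI. The adult targets are 13 percentage points and 1.7 BMI units, with 80% power at 0.05.

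No section names a group-by-wave term, a change contrast or adjustment for the 2008/9 level of the outcome.

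**The concern.** Without randomisation, nothing makes the intervention and comparison groups equal in expectation on weight status or behaviour before the intervention. A post-intervention contrast then estimates the intervention effect plus the pre-existing difference that matching and covariates have not removed. The two parts cannot be separated within the 2010 data, and the confidence interval does not reflect the second.

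Table 1 adds to the problem. Two communities have primary-age or younger children as their primary target, two have secondary students, and one has working adults. With so few communities per age group, local peculiarities have little chance to average out.

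The error can go either way: an apparent benefit where there is none, or a real benefit hidden. The 2008/9 wave, which would show the difference and allow it to be subtracted, is measured in both groups but has no stated role in the primary estimate.

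**Working it through.** **1. The plan's own figure.** The adult sample is 245 per group. For BMI, n = 2 × (SD × 2.80 / 1.7)². This gives 244 if SD = 6.7 with no design effect, and 136 if SD = 5, for which 245 implies a design effect of 245/136 = 1.8. For 13 points, a continuity-corrected calculation gives 243-247 at assumed base rates of 40-50%. So 245 is attainable, but it cannot be confirmed because no SD, base rate or intracluster correlation is given. The point does not depend on it.

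**2. Standard errors implied by the targets.** SE = target / (1.960 + 0.842).
- Students: 0.15 / 2.80 = 0.0535 zBMI. Power of 80% and two-sided 5% are assumed, because the article attaches these values only to adults.
- Adults: 1.7 / 2.80 = 0.61 BMI units. Two-sided testing is assumed.

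**3. False-positive rate with no true effect.** For a residual pre-existing difference b, P(reject) = Φ(b/SE − 1.96) + Φ(−b/SE − 1.96).

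| Group | b | b/SE | P(reject) |
|---|---|---|---|
| Students | 0.05 zBMI | 0.93 | 15% |
| Students | 0.10 zBMI | 1.87 | 46% |
| Adults | 0.5 BMI units | 0.82 | 13% |
| Adults | 1.0 BMI units | 1.65 | 38% |

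As a fraction of the target effect, a quarter gives 10.8% and a half gives 29%. The reverse also holds. If the true effect is 0.15 zBMI and a residual 0.05 favours the comparison group, the net difference is 0.10 and power falls from 80% to 46%.

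**4. Precision of a change contrast, students.** With an assumed zBMI SD of 1.0, n = 2 × (2.80 / 0.15)² = 698 per group without clustering. Half of 2,400 primary students is 1,200, so the implied design effect is 1,200 / 698 = 1.72 (equal groups, 2,400 per wave). Let r be the correlation of the underlying school effects across waves. The variance of the change contrast relative to the 2010-only contrast is 2 × (1 + 0.72 × (1 − r)) / 1.72.

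| r | Variance ratio | Detectable zBMI (0.15 × √ratio) | Power at 0.15 |
|---|---|---|---|
| 0.8 | 1.33 | 0.173 | 68% |
| 0.5 | 1.58 | 0.189 | 61% |
| 0 | 2.00 | 0.212 | 51% |

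In terms of the correlation ρ of the observed school means, the ratio is 2(1 − ρ), with ρ = r × 0.72 / 1.72. At r = 0.5, ρ = 0.21 and the ratio is again 1.58. The change contrast costs no precision only if ρ reaches 0.5.

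**5. Precision, adults, independent waves.** 1.7 × √2 = 2.4 BMI units and 13 × √2 = 18.4 points. Power at the original targets is about 51%. Restoring 80% would take 245 × 2 = 490 per group per wave.

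**The case against.** Four arguments deserve weight.

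**Confounding is already addressed.** A reader might infer that every pre-existing difference is counted in full as an intervention effect. The article does not support that. Comparison schools are drawn at random from schools matched on type, size, disadvantage and location. Demographics are adjusted for, with the named ones only examples, and Census variables such as income and education enter the models. The part of a difference that these explain is removed. What stands is that none of them names the outcome at baseline, so the residual goes through.

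**The article is condensed.** It does not say that the 2010 wave is used alone, and a fuller plan might adjust for 2008/9 means. But this sentence fixes the primary contrast rather than leaving it open, and a post-only comparison is its natural reading.

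**The sample-size text is not a contradiction.** A reader might infer a conflict from the mention of change. The following sentence defines the target as a between-group difference, which fits the stated primary analysis. This is a poor choice of estimand, not an internal inconsistency.

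**A change contrast has its own weaknesses.** It assumes parallel trends. The projects were also under way before the evaluation was funded (Preparation for evaluation), so 2008/9 may already contain some early effect, which subtraction would remove. Both caveats stand. They are reasons to keep the 2010-only estimate as secondary, but not to leave baseline out of the primary one.

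**Conclusion.** The point holds for residual differences. As written, the primary analysis lets any pre-existing difference in the outcome that survives matching and covariate adjustment pass one-for-one into the effect estimate, although data to correct for it are collected in the same schools and workplaces. Following individuals is not required: repeat cross-sections in the same clusters support a change contrast.

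The 15% and 46% (students) and 13% and 38% (adults) are illustrations. They rest on the assumed student power and two-sided testing, and on residual differences chosen for the purpose. The article gives no observed imbalance, so it cannot be inferred that a false positive is likely in this study. Nor should weight be put on a residual of 0.15 zBMI giving 80%: a bias equal to the design target is rejected at the design power by construction.

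The primary analysis should be changed, because a loss of precision shows in the confidence interval and residual confounding does not.

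**What to change.** 1. Define the primary estimate as the group-by-wave interaction, that is, the difference in change from 2008/9 to 2010. Fit one model to both waves, clustered on school or workplace, with the demographic and community covariates already planned.
2. At a minimum, adjust the 2010 comparison for each school's or workplace's own 2008/9 mean. This corrects only partly, because those means are measured with error.
3. Keep the 2010-only comparison as a secondary analysis.
4. Do not rely on community as a clustering level. With one or two intervention communities per primary target age group, between-community variance is barely estimable, and for working adults not estimable on the intervention side. State this as a limitation.
5. State the parallel-trends assumption, and that the change contrast may be conservative if 2008/9 already holds early effects.
6. Restate the detectable differences for the new estimate, with the assumed between-wave correlation.

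**Cost.** No new data are needed, but there is a real loss of precision. Detectable zBMI becomes about 0.17-0.19 if school effects correlate 0.5-0.8 across waves (design effect 1.72 assumed). The worst case, with independent waves, is about 0.21 zBMI, 2.4 adult BMI units and 18 percentage points.
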